### Aims

Overall, this study aims to evaluate the implementation of a CCDSS in HMRs to deprescribe medications, particularly those with anticholinergic and sedative effects, and to assess the effect of deprescribing on prescribing and clinical outcomes. Specifically, this study will aim to:
Reduce the proportion of patients who are exposed to anticholinergic and sedative medications as measured by the DBI;Examine the effect on clinical outcomes (including cognitive and physical function, falls, and institutionalisation), and mortality;Examine the effect on patient process outcomes (including adherence and physician visits)Evaluate the process of implementing a CCDSS intervention within HMR.

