#### Outcomes and follow-up

The primary outcome will be any reduction of anticholinergic and/or sedative medication use, as measured by DBI, between baseline and 3-months (binary outcome). Previous studies consistently observe an association between increasing DBI and impaired physical function [29]. The degree of exposure that results in a clinically significant change has been estimated to be a difference in DBI of approximately 0.5 [44]. Our previous study found that DBI is reduced in usual care HMR in 8.9% of patients by a median value of 0.28 [45], and an increase in this proportion by 10% was seen as a clinically meaningful effect on a population level. It was not feasible to power the study to primarily investigate impact on multifactorial measures of physical function.

Secondary outcomes will include:
Recommendations to reduce anticholinergic and or sedative medications as measured by DBI in the HMR report and/or the G-MEDSS report;Prevalence of deprescribing (cessation and/or dose reduction) any medicationChanges in clinical outcomes (physical function, cognitive function, falls, and institutionalisation)Changes in patient process outcomes (medication adherence and physician visits)Mortality at 3-monthsA subgroup analysis (of the above outcomes) for people living with and without dementia

All ACPs will be required to collect additional information of their HMR recipients at baseline (during HMR interview) and at a 3-month follow-up visit. The 3-month follow-up has been added exclusively to this study for the purposes of data collection as the HMR process (usual care) does not involve a follow-up visit. The following outcomes will be assessed of the patient participants enrolled in the study: medication adherence, cognitive impairment, functional status, falls, institutionalisation and the number of physician visits. Mortality data will be captured by the ACP participants at 3-month follow-up (Table 1).

**Table 1 Tab1:** Patient participant data to be collected during the study

	Measure (s)	Baseline^a^	3-months
Demographics			
Age		✓	
Sex		✓	
Ethnicity		✓	
Marital Status		✓	
Education Status		✓	
Geographic remoteness/locality	PhARIA	✓	
Medication Profile			
Current medication list (prescribed, OTC and complementary, regular or PRN)		✓	
Changes to medication list (e.g. additions, cessations, ↑↓dose)			✓
Ceased medications		✓	✓
Adherence	MGL	✓	✓
Attitudes towards deprescribing^b^	rPATD, rPATDCog	✓	
Anticholinergic and sedative burden	DBI	✓	✓

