Comorbidity and Physical Function			
Comorbidities	FCI	✓	✓
Cognition	Mini-Cog© [46]	✓	✓
Independent activities of daily living	NHCCSFSI	✓	✓
Physical Function	SPPB	✓	✓
Falls History		✓	✓
Others			
Institutionalisation (e.g. hospitalisation)		✓	✓
Physician visits (e.g. GP or specialist appointments)			✓
Mortality			✓
Goals of care^b^		✓	

^a^at the time of the HMR interview; ^b^only for patients in the intervention arm of the study

*PhARIA* The Pharmacy Access/Remoteness Index of Australia – quantifies degree of remoteness (geographic and professional) [47], *OTC* Over-the-counter, *PRN* when required, *MGL* Morisky, Green, Levine Scale [48], *rPATD* revised Patients’ Attitudes Towards Deprescribing [34], *rPATDCog* Revised Patients’ Attitudes Towards Deprescribing for people with Cognitive impairment [35], *DBI* Drug Burden Index [28], *FCI* Functional Comorbidities Index [49], *NHCCSFSI* National Home and Community Care Services Functional Screening Instrument [50], *SPPB* Short Physical Performance Battery [51], *GP* General practitioner

↑↓ = changes

The Morisky Green Levine Scale will be used to measure self-reported patient medication adherence [48]. Cognitive impairment will be assessed using the Mini-Cog© [46, 52–54]. The National Home and Community Care services Functional Screening Instrument (NHCCSFSI) (part one) and the Short Physical Performance Battery (SPPB) will be used to assess the functional status of patient participants [50, 51]. Details regarding scoring of these measures used in this study can be found in Additional file 1.

Data to calculate the Functional Comorbidity Index (FCI) will be collected from the patients. The FCI is a sum of 18 self-reported comorbid conditions with a score of 0–18. The FCI will also be used to measure comorbidities that predict physical function in older adults. A higher FCI score indicates greater morbidity and is associated with poorer physical function [49].

Falls (any fall in the last 12 months at baseline and number of falls at 3-months), institutionalisation (admission to hospital in the last 12 months at baseline and number of days admitted to hospital, nursing home or respite care at 3-months) and the number of physician visits (GP and specialist) will be captured over 3 months by providing patients and/or their carers a calendar to self-record events that will be collected by ACPs.

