#### Statistical analyses

The primary analyses will be conducted using an ‘intention-to-treat’ approach and will be reported according to the guidelines of the Consolidated Standards of Reporting Trials (CONSORT) 2010 statement. Descriptive statistics (means and proportions) will be used to report the demographics of the study populations (ACPs and patient participants) at baseline. Binary continuous and count outcomes will be analysed using logistic, linear and negative binomial regression models, respectively. All models will include a covariate for the intervention group, with a random effect for the clusters (ACPs). Analyses will provide an estimate of the difference between groups, 95% confidence intervals (CI) and *p*-values. All statistical tests will be two-tailed, and p-values of < 0.05 will be deemed statistically significant. Appropriate model checking will be conducted. The statistician performing the data analysis will be blinded to the identity of each treatment group.

Secondary analyses will include:
Where appropriate, to conduct further adjusted analyses, covariates will be included for the patients’ baseline value (for that outcome) and any baseline characteristic for which there is evidence of imbalance between intervention and comparison groups;A subgroup analysis for people living with dementia;For clinical outcomes, assessments of associations between change in DBI or a deprescribing of a medication, using the same statistical methods as described above, but with the intervention group removed from the model and replaced by change in DBI or deprescribing of medication;Association between rPATD and deprescribing in overall patient population.

To analyse the responses to the rPATD questionnaire, factor scores will be created for each of the 4 factors (appropriateness, burden, concerns about stopping and involvement) as previously described [34]. Likert responses to the global question ‘I would be willing to stop one or more of my medications if my doctor said it was possible’ will be dichotomised into those that agree (strongly agree and agree) and those that are unsure/disagree (unsure, disagree, strongly disagree). Factor scores and responses to the global questions will be compared to deprescribing outcomes (DBI and prevalence of deprescribing) using Mann-Whitney and χ^2^ tests.

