## Discussion

There is a current need to optimise deprescribing of inappropriate medications in older adults and it is important to involve collaboration with patients within this process [60]. CCDSS for medication management can be considered an effective method for reducing inappropriate prescribing and ADEs in older adults, however there is limited data on the real effect on patient outcomes [61]. Consolidating patient preferences and perspectives on outcomes and goals of therapy is important to guide decisions to reduce or stop medications [62]. There is limited evidence on the effect of goal-directed medication management on prescribing and clinical outcomes. The G-MEDSS is a novel CCDSS intervention that provides clinical decision support for healthcare practitioners, incorporating the patients’ goals and preferences during the medication review process. This study aims to evaluate the implementation of a CCDSS in HMRs to deprescribe medications, and to assess the effect of deprescribing on clinical outcomes.

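### The aim of assessing the effect of deprescribing on clinical outcomes has no randomised analysis behind it: the only model with deprescribing as exposure is a secondary association that drops the randomised arm and is open to confounding and reverse causation

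*Protocol article*

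**What the plan says.** The Aims section gives the overall purpose as evaluating the decision support system and "to assess the effect of deprescribing on prescribing and clinical outcomes". The Discussion repeats it as "to assess the effect of deprescribing on clinical outcomes", and the abstract uses the same wording.

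Under Statistical analyses, binary, continuous and count outcomes go to logistic, linear and negative binomial regression. The general rule is "All models will include a covariate for the intervention group, with a random effect for the clusters (ACPs"). Among the secondary analyses is a further item: "For clinical outcomes, assessments of associations between change in DBI or a deprescribing of a medication", with the same methods, "but with the intervention group removed from the model and replaced by change in DBI or deprescribing of medication".

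An earlier item in that list allows adjusted analyses, where appropriate, for the baseline value of the outcome and "any baseline characteristic for which there is evidence of imbalance between intervention and comparison groups".

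Under Outcomes and follow-up, the reduction in DBI is assessed "as measured by DBI, between baseline and 3-months (binary outcome"). Falls, institutionalisation and physician visits "will be captured over 3 months by providing patients and/or their carers a calendar to self-record events".

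**The concern.** The trial randomises pharmacists to use G-MEDSS or not. It does not randomise deprescribing. A comparison of arms on function, cognition, falls or institutionalisation therefore estimates the effect of offering G-MEDSS. An aim worded as the effect of deprescribing asks a different question, and the only model that addresses it gives up the protection of randomisation.

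If the wording of the aim and the output of that model meet in the final report, readers may take a confounded association as evidence that reducing sedative and anticholinergic drugs harms or helps patients. The Limitations section warns of low power for clinical outcomes. It does not mention confounding or reverse causation in this analysis.

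**Working it through.** No figure in the plan bears on this analysis; the sample size of 500 is set for the primary outcome. The check is first a reading of the sections together, then an illustration under stated assumptions.

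**1. Time order.** Change in DBI runs from baseline to 3 months. Falls and institutional days are counted over the same 3 months, and function and cognition are measured at the same two visits. No order between exposure and outcome is stated. A fall in week 4 that leads to a drug being stopped in week 5 counts as an outcome of the stopping.

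**2. Baseline burden.** The Background says that rising DBI goes with poorer function, falls, frailty, hospitalisation and death. Eligibility does not require a DBI above zero, and a patient at zero cannot reduce it. Reducers therefore come from the part of the sample with worse expected outcomes. Baseline DBI is not a named term.

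**3. The covariate rule.** Even if the adjusted-analysis item carries over, it asks whether the arms differ, not whether deprescribed and other patients differ. A strong driver of deprescribing that is well balanced by arm would be left out.

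**4. Dropping arm.** Use the planning figures: 500 patients in equal arms, with reductions in 20% and 10%.
- Reducers: 250 × 0.20 + 250 × 0.10 = 50 + 25 = 75, of whom 50/75 = 66.7% are in the intervention arm.
- Non-reducers: 200 + 225 = 425, of whom 200/425 = 47.1% are in the intervention arm.

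The intervention also delivers goals of care, attitudes to deprescribing and patient reports, and outcomes are collected by unblinded pharmacists. In a simple unadjusted comparison, 0.667 − 0.471 = 0.196 of any arm difference from those routes would pass to the deprescribing coefficient.

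**5. Illustration of reverse causation (all inputs assumed).** Let 15% of patients fall within 3 months. Let deprescribing occur in 15% of non-fallers and 30% of fallers because the fall prompts it. Deprescribing has no effect.
- Odds ratio = (0.30/0.70)/(0.15/0.85) = 2.43.
- Fall risk if deprescribed = 0.15 × 0.30/(0.15 × 0.30 + 0.85 × 0.15) = 0.045/0.1725 = 26.1%.
- Fall risk otherwise = 0.15 × 0.70/(0.15 × 0.70 + 0.85 × 0.85) = 0.105/0.8275 = 12.7%.
- With 22.5% in fallers instead of 30%, the odds ratio is (0.225/0.775)/(0.15/0.85) = 1.65 (20.9% v 13.9%).

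**6. Simulation (strengths assumed).** 100 pharmacists × 5 patients, ICC 0.07, deprescribing about 20% v 10%, a continuous outcome, true effect zero, 4,000 runs per row. Arms were compared on pharmacist means. The arm-removed model was linear regression with cluster-robust errors and no baseline covariates, a stand-in for the planned random-effect model.

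| Scenario | Rejections, by arm | Rejections, arm removed | Spurious difference, arm removed (SD) |
|---|---|---|---|
| Neither problem | 4.6% | 4.6% | 0.00 |
| Common cause: 0.1 SD on outcome, log-odds 0.2 on deprescribing | 4.8% | 5.6% | 0.02 |
| Common cause: 0.2 SD, log-odds 0.4 | 5.7% | 9.2% | 0.08 |
| Common cause: 0.3 SD, log-odds 0.6 | 4.9% | 28.5% | 0.17 |
| Outcome shifts log-odds of deprescribing by 0.2 per SD | 5.4% | 36.8% | −0.21 |
| Outcome shifts log-odds by 0.4 per SD | 5.0% | 88.8% | −0.41 |

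The comparison by arm stays near 5% throughout. The arm-removed model does so only when both problems are absent or weak.

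**The case against.** A reader might infer that the trial's whole answer on clinical outcomes rests on the arm-removed model. The document does not support that. Clinical outcomes are listed as secondary outcomes and are analysed with the randomised arm in the model. The arm-removed model is an extra secondary item, the article already calls it an association, and nothing says that it answers the aim. Leaving arm out is an explicit exception to the general modelling rule and not a contradiction of it.

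A reader might also infer that the model would contain only the exposure and the pharmacist effect. That is one reading. The reference back to the methods above could bring in the baseline value of the outcome. A full covariate list can fairly be left to an analysis plan.

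Nor is the odds ratio of 2.4 an estimate of the bias in this trial. It is a two-by-two calculation on invented rates, whereas the number of falls would go to negative binomial regression and give a rate ratio.

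All of this stands, and it narrows the point. It does not remove it. The association label does not fit an aim worded as an effect in three places. The one covariate rule that the article does state is aimed at the wrong contrast. The shared window is fixed by the design and not by a detail left for later.

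**Conclusion.** The point holds in a limited form. The aim as worded goes beyond what the design can show: the randomised comparison gives the effect of G-MEDSS, and the only model with deprescribing as exposure can show an association where there is no effect. The mechanism follows from the stated windows, the removal of arm and the covariate rule. The size does not; the figures above rest on assumed strengths, and the false-positive rate ran from close to nominal (5.6%) to 88.8% as these varied. The primary outcome and all comparisons by arm are untouched. This is an inexpensive improvement to the wording of an aim and to one secondary analysis.

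**What to change.** 1. Word the clinical-outcome aim, in the abstract, Aims and Discussion, as the effect of G-MEDSS, and base any statement of effect on the randomised comparison.
2. Label the deprescribing model exploratory and non-causal.
3. In that model keep arm, and prespecify baseline DBI, the baseline value of the outcome, age and the Functional Comorbidity Index, all collected under Table 1. Add dementia status where recorded. For falls and hospital admission, the baseline value is the 12-month history.
4. State that reverse causation cannot be excluded, because exposure and outcome share the same 3 months.

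Do not try to solve the timing problem by counting only events after the medication change, unless a common index date is defined for all patients. Otherwise deprescribed patients have shorter follow-up and patients without a change have no start date, which brings in immortal-time bias. It would not help function or cognition, which are assessed only at the two visits, and Table 1 does not list dates of medication change.

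The cost is a few more model terms and some rewording, with no new visits. Keeping arm and adding covariates lessens confounding but does not remove it, and does nothing about reverse causation.

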**Fig. 1 Fig1:**
[figure not shown]
The process of a Home Medicines Review (HMR) in Australia. ACP = Accredited Clinical Pharmacist; GP = General Practitioner. *For a patient to be eligible for a HMR they must: be a current Australian Medicare/Department of Veterans’ Affairs cardholder, live in a community setting, and be at risk of experiencing medication misadventure as determined by their prescribing doctor [16].

Computerised Clinical Decision Support Systems (CCDSS) have the potential to improve GPs’ and pharmacists’ decision-making during the medication review process [21]. CCDSS apply algorithms to individual patient data to improve clinical decision making and optimise health outcomes, and may be considered as an enabler to deprescribing [22, 23]. For example, an interventional study of patients in a geriatric ward in Italy evaluated the effectiveness of a CCDSS in reducing potentially inappropriate medications. The use of a CCDSS in this study was associated with a significant reduction in potentially inappropriate medications and new onset of severe drug-drug interactions [24]. In a recent study, integration of a CCDSS into HMR was demonstrated as a feasible and useful method to prompt deprescribing of anticholinergic and sedative medications in older adults [25]. Although the implementation of CCDSS interventions into practice have improved medication prescribing, the magnitude of the effect is varied according to study design, and only a limited number of studies reported improved clinical outcomes [26, 27]. Furthermore, CCDSS platforms allow the incorporation of various validated tools to support practitioners when deprescribing. These can include tools to identify inappropriate medications, enhance shared decision-making and support goal-directed care.

The Drug Burden Index (DBI) was developed to pharmacologically measure the cumulative exposure of older adults to anticholinergic and sedative medications and relate this exposure to physical and cognitive function [28]. Increasing DBI scores have been associated with poorer physical function, falls, frailty, hospitalisation and mortality in older adults [29, 30]. The DBI Calculator© was developed as a reliable and valid CCDSS to report DBI of older patients taking multiple medications [31]. The DBI Calculator was recently investigated as a CCDSS in the HMR setting and demonstrated that it was a feasible and useful method to prompt deprescribing in older adults [25].

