#### Sample size

The sample size calculation for this study is based on a feasibility study of implementing The Drug Burden Index Calculator© report into the HMR service [25]. In the feasibility study, 18 pharmacists recruited 100 patients (average cluster size 5.6) where 25 (25%) patients had a reduction in their DBI score, 7 (7%) patients had an increase in their DBI score, whilst the remaining 68 (68%) had no change in DBI score. The estimated intra-cluster correlation (ICC) was 0.07. With a sample size of 500 participants, we will have 80% power to detect a 10% difference between the intervention and comparison groups, corresponding to 20% of participants in the intervention group and 10% of participants in the comparison group having a reduction in DBI, assuming a 5% significance level (two-sided) and an Intra-cluster Correlation Coefficient (ICC) = 0.07. This corresponds to a relative reduction of 2, therefore we will be powered to detect a difference corresponding to twice the reduction in the intervention compared to the control.

As of March 2017, there were 2374 general registered ACPs practising in Australia. To reach the estimated clustered sample size of 500 patients, approximately 120 pharmacists will need to be recruited, 60 pharmacist participants in each of the intervention and comparison groups (allowing for 20% dropout rate – estimate based on the previous study [25]). Each ACP will be required to recruit 5–10 participants to achieve an average of 5 patients per ACP (total of 500 patients).

Using published national statistics, we estimate that 10–31% (*n* = 50–155) of recruited patients will have a diagnosis of dementia and subgroup analyses is planned on these participants [10].

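### The secondary models of clinical outcomes on change in DBI choose covariates by imbalance between randomised arms, so baseline DBI, a built-in confounder of this exposure, is not adjusted for by rule

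*Protocol article*

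**What the plan says.** The Statistical analyses section first sets out the main models: "All models will include a covariate for the intervention group", together with a random effect for the pharmacist. Clinical outcomes get this arm-based comparison. The list of secondary analyses then adds two relevant items:

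- Adjusted analyses, where appropriate, with the patient's "baseline value (for that outcome") and any baseline characteristic showing imbalance between the intervention and comparison groups.
- For clinical outcomes, assessments of associations by the same methods, but "with the intervention group removed from the model and replaced by change in DBI or deprescribing of medication".

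Baseline DBI is collected (Table 1) but is not named as a covariate for these models. The Background states that "Increasing DBI scores have been associated with poorer physical function, falls, frailty, hospitalisation and mortality in older adults".

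On timing, Outcomes and follow-up defines the DBI endpoint as "any reduction of anticholinergic and/or sedative medication use, as measured by DBI, between baseline and 3-months". Falls are recorded as "any fall in the last 12 months at baseline and number of falls at 3-months". Falls, institutionalisation (as days in hospital, nursing home or respite care) and physician visits are "captured over 3 months by providing patients and/or their carers a calendar to self-record events".

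**The concern.** Choosing covariates by imbalance between arms makes sense when arm is the exposure. Once arm is replaced by change in DBI, the confounders that matter are those that differ between patients whose DBI fell and patients whose DBI did not. The rule never looks at that contrast.

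Baseline DBI is the clearest such confounder. It determines who can have a reduction at all, and the protocol itself ties it to the outcomes being modelled. The outcome's own baseline value is only a partial substitute. For falls it is a yes/no item covering the previous 12 months.

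A second problem concerns falls and days institutionalised. A fall or admission inside the 3 months can prompt a medicine to be stopped or started, and the model would then count the consequence of the event as its exposure.

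The Abstract, Aims and Discussion speak of assessing the effect of deprescribing on clinical outcomes. These are the only planned clinical-outcome models with deprescribing itself as the exposure, and they carry the same confidence intervals and 5% threshold. A spurious association could therefore be reported against that aim.

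**Working it through.** **Plan's own figures.** The protocol gives no figure for these models, and its sample size is not in question.

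**Inputs from the document.** Sample size assumes 20% and 10% with a DBI reduction. With 250 per arm, 250 × 0.20 + 250 × 0.10 = 75 of 500, or 15%. The median reduction in usual care is 0.28 (Outcomes and follow-up). In the feasibility study, "7 (7%) patients had an increase in their DBI score" out of 100.

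**Assumed inputs (none is in the document).** h = share with baseline DBI above 0 (0.5–0.7); k = their fall rate relative to DBI 0 (1.25–2.0); f = share falling within 3 months (0.10–0.20); s = share of fallers with DBI above 0, and not otherwise reduced, who have a DBI medicine cut because of the fall. The true effect of deprescribing is set to none.

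**Step 1: baseline DBI omitted.** Every reduced patient has DBI above 0, so their relative fall rate is k. The other 85% mix (h − 0.15) at rate k with (1 − h) at rate 1. The false rate ratio is

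RR = k / {[(h − 0.15)k + (1 − h)] / 0.85}

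- h 0.7, k 1.25: 1.25 / (0.9875/0.85) = 1.08
- h 0.6, k 1.5: 1.5 / (1.075/0.85) = 1.19
- h 0.5, k 2.0: 2.0 / (1.2/0.85) = 1.42

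The same cases were simulated with 1.5 million patients (negative binomial, dispersion 1.5, f = 0.15, about 39% with a fall in the prior year). Adjusting for any prior-year fall, as the optional rule would, leaves about 1.05, 1.12 and 1.25. Adding an indicator of baseline DBI above 0 returns about 1.00 in all three.

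This assumes that, among patients with DBI above 0, reduction does not depend on the level. A separate simulation let the chance of reduction rise with DBI (35% at DBI 0, mean 0.8 otherwise) and the fall rate rise by a factor of exp(0.25), exp(0.5) or exp(0.75) per DBI unit. It gave 1.15, 1.40 and 1.68 without baseline DBI, and about 0.98 with it. The first range is thus not an upper bound, and the level of DBI should be a covariate even after restriction.

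**Step 2: shared 3-month window.** With x = s(h − 0.15), and no baseline confounding,

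RR = {(0.15 + x)/(0.15 + fx)} / {(0.85 − x)/(0.85 − fx)}

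At h 0.6, f 0.15, s 10%: x = 0.045, so (0.195/0.15675)/(0.805/0.84325) = 1.30. At s = 5% it is 1.15 and at 20% it is 1.62. The 1.30 comes from 500 × 0.15 × 0.10 × 0.45 = 3.4 patients.

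Restricting to DBI above 0 does not help. The reduced share becomes 0.15/0.6 = 0.25, and (0.325/0.26125)/(0.675/0.73875) = 1.36.

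**Step 3: direction.** With continuous change in DBI (steps of 0.28, 15% reduced, 7% raised, h 0.6, f 0.15, s 10%), the simulated rate ratio per 0.28 reduction is about 1.18 if no faller is started on a DBI medicine, 0.96 if 6% are and 0.85 if 10% are. The net sign depends on stops against starts, which the document does not give.

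**The case against.** **The wording is modest.** The protocol calls these analyses associations and lists them as secondary. It gives clinical outcomes an arm-based model first, and Limitations warns that the trial is not powered for them. A reader might infer that the protocol presents these models as proof of an effect. It does not: linking the general aim to this item is an inference, and the specific aims can be read as served by the randomised comparison. What stands is that an association still needs its obvious confounder, and Limitations mentions neither confounding nor reverse causation here.

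**A fuller analysis plan may exist.** Restrictions and sensitivity analyses are often left to it, and the where-appropriate clause does not forbid baseline DBI. But the article does state a covariate rule, and that rule is tied to the wrong contrast. Correcting it is different from asking for missing detail.

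**The distortion may be hard to see at this sample size.** In simulated trials of 500 adjusted for prior fall, the three Step 1 cases reject a true null in roughly 5%, 5–7% and 10–17% of trials, depending on set-up. This is fair: in the low and middle cases the bias would seldom produce a significant result. The estimate and its interval are still shifted.

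**Scope.** Three wider readings are not supported:

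- Physician visits are process outcomes in Aims and in Outcomes and follow-up. They come under these models only if classed as clinical, as the Abstract does with GP visits.
- Institutionalisation is counted in days, so the point is not about admission counts.
- Deprescribing of any medication is possible at DBI 0, so the structural argument does not extend to that exposure.

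**Conclusion.** The point holds for the change-in-DBI models of clinical outcomes. Followed as written, the covariate rule leaves baseline DBI out except by chance, and the resulting associations are confounded by it. Under the assumed inputs, a null effect on falls would appear as a rate ratio of 1.08–1.42 unadjusted, or 1.05–1.25 after adjustment for a prior-year fall, making DBI reduction look harmful. Every size here rests on assumptions about the DBI distribution and fall rates; the structural dependence and the link with outcomes come from the protocol.

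For falls and days institutionalised, the shared window adds reverse causation of unknown size and, for continuous change in DBI, unknown sign. These associations are exploratory.

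A reader might go further and infer that the trial's evidence on clinical outcomes is compromised. It is not: the primary outcome and all between-arm comparisons are unaffected. The change is worth making because it is nearly free, not because a main result is at risk.

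**What to change.** In Statistical analyses:

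1. Include baseline DBI and, where collected, the outcome's baseline value in every change-in-DBI model, whatever the balance between arms.
2. Restrict any binary DBI-reduction model to patients with baseline DBI above 0, keeping baseline DBI as a covariate.
3. For any-medication deprescribing, add baseline DBI as a sensible covariate, without the restriction.
4. State that the associations for falls and days institutionalised are exploratory because exposure and events share the same 3 months, and that effects on clinical outcomes are judged from the randomised comparison. Apply the same caveat to physician visits if they are analysed as a clinical outcome.

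The document does not show that dates of medicine changes are held. If they are, a sensitivity analysis counting only events after the change could be added; if not, item 4 suffices.

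The cost is a few sentences. Baseline DBI is already in Table 1. The restriction drops 30–50% of patients from the DBI-reduction models under the assumed shares, all of them patients who could not have had a reduction.
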